## Abstract

**Background:**

Pregnancy-related posterior pelvic girdle pain (PPGP) is one of the most important clinical manifestations of postpartum back pain. Those affected often complain of discomfort during daily activities. It is hypothesized that altered motor control is associated with perceived pain. Pelvic support can regulate possible underlying altered motor control mechanisms and decrease pain. However, the influence of a lumbosacral orthosis, which is broader support that allows for a wider contact area and more skin sensory stimulation to restore proper motor function, has not yet been investigated in women with postpartum PPGP.

**Objective:**

This study investigates the efficacy of broader lumbar support and narrower pelvic support on pain, proprioception, disability, and muscle strength in women with pregnancy-related PPGP.

**Methods:**

This study will be a single-center, 3-armed, participant-blinded, randomized controlled trial. In total, 84 women diagnosed with pregnancy-related PPGP will be recruited and randomly assigned into 3 groups. Intervention groups A and B will receive pelvic and lumbar supports, respectively. Group C (control) will receive only a patient education leaflet containing advice on strengthening exercises, comfortable positions, and other practical information. The study outcomes are pain, effort score during the active straight leg raising test, maximum isometric hip flexion force, maximum isometric hip external rotation force, maximum isometric trunk rotation force, and joint position reproduction of hip abduction. The study outcomes will be measured at 4 time points: baseline (T1), immediately after the intervention (T2), 4 weeks following interventions began (at this time, the intervention period is completed) (T3), and 1 week after discontinuing the interventions (T4) to evaluate the possible lasting effects of wearing supports. Multivariate analysis of variance will be used to test between- and within-group differences.

**Results:**

Recruitment for this study will be started in summer 2022 and is expected to be completed by the end of fall 2022.

**Conclusions:**

This study will examine the efficacy of broader lumbar support as an early rehabilitative treatment for women receiving postpartum posterior pelvic pain support compared to those receiving a narrower pelvic support. We expect the broader lumbar support to impact pain management and disability better than the current narrower pelvic belt. Long-term follow-up studies will help determine whether such lumbosacral orthosis reduces pain and improves daily activities in women with pregnancy-related PPGP.

**Trial Registration:**

Iranian Registry of Clinical Trials IRCT20150210021034N11; https://www.irct.ir/trial/54808

**International Registered Report Identifier (IRRID):**

PRR1-10.2196/40553

## Introduction

Pregnancy-related posterior pelvic girdle pain (PPGP) is a common musculoskeletal disorder affecting women’s well-being in the postpartum period [1]**.** Nearly half of the involved population demonstrates moderate to severe disability [2]. This painful condition is related to physical and psychosocial aspects, including kinesiophobia, psychological distress, beliefs regarding curability, financial stress, and social isolation [3-6]. The alteration of motor control in people with pelvic pain has been documented [7] and can affect a change in the load transfer ability at the pelvis [8]. Pregnancy-related PPGP is commonly localized in the vicinity of the sacroiliac joint (SIJ) [9]. One of the SIJ’s functions is transmitting the upper body weight to the pelvis and lower extremities and vice versa [10]. Dynamic control of mechanical and neural systems acting on the pelvis allows the lumbopelvic movements to be smooth, painless, and effortless under changing conditions [11]. Pregnancy-related PPGP includes the dysfunction of sensorimotor pathways that control load transfer through the SIJ [11,12]. The altered spinal and abdominal muscle activations and perceived pain affect the function of the SIJ in postnatal women [13]. Those with pregnancy-related PPGP often complain of discomfort during load transfer tasks through the pelvis [14]. The active straight leg raise (ASLR), as a biomechanical test, is proposed to check load transfer between the spine and legs via the pelvis [14,15].

Many preventive or therapeutic strategies are used for the management of pregnancy-related PPGP. Current pain relief recommendations include avoiding certain physical loads, relaxation, massage, medications, exercise, physical therapy, and pelvic or lumbar supports [16]. Among the recommendations for managing pregnancy-related PPGP, it was noted that pelvic or lumbar support is widely used to manage painful symptoms [17,18]. Pelvic or lumbar support, also known as soft orthosis, can work through a combination of mechanisms to address the SIJ instability. First, the circumferential supports are expected to apply a compressive force on the pelvis to promote anatomical alignment [19], stiffness [20], and increase the function of the SIJ [21]. Second, soft orthoses can also provide potent stimuli to improve neuromuscular control required for lumbopelvic function [22]. It has been shown that the gentle pressure soft orthoses applied to the skin receptors can positively affect proprioceptive acuity [20,23], pain intensity [17,24], joint stability [25,26], and physical function [17,27].

Emerging research has highlighted the sensorimotor effectiveness of narrow pelvic supports in pregnancy-related PPGP [27,28]. Furthermore, previous research has indicated that lumbar support effectively improved proprioceptive awareness in healthy subjects [22]. However, the effect of broader lumbar supports that allow for a wider contact area and greater skin sensory stimulation in women with pregnancy-related PPGP remains unclear. Therefore, this study first aims to investigate whether using lumbar support reduces pain in women with pregnancy-related PPGP versus controls. Secondly, it aims to examine whether broader lumbar support is more beneficial than narrower pelvic support on disability and sensorimotor outcomes (eg, joint positions reproduction) in the lumbopelvic area in women with pregnancy-related PPGP.

## Methods

### Study Design

A prospective 3-armed, participant-blinded, randomized controlled trial (interventions versus control group) will be performed to investigate the aims. The Template for Intervention Description and Replication (TIDieR) checklist and related guidelines will be used to report the study process [29,30]. The TIDieR checklist describes a standard way to document details carefully and allows authors to write interventions in their studies clearly [29]. The CONSORT-EHEALTH (Consolidated Standards of Reporting Trials of Electronic and Mobile Health Applications and onLine TeleHealth) checklist will be used to report data efficiently as an eHealth intervention trial [31].

### Setting

Participants will be recruited from Isfahan University of Medical Sciences (IUMS), Isfahan, Iran.

### Ethics Approval

The local ethical committee of IUMS approved the study protocol (IR.MUI.NUREMA.REC.1400.007). The study protocol was registered in the Iranian Registry of Clinical Trials on April 31, 2021 (IRCT20150210021034N11).

### Sample Size

In total, 84 women with postpartum PPGP will be recruited. The optimal sample size was calculated on the basis of the results of a previous study [32]. The pain intensity for intervention groups was 58.2 (SD 13.93) and 64.4 (SD 13.96) at baseline, respectively [32]. We estimated a sample size of 25 in each study arm, which would yield 60% power (α=.1) and an effect size of 0.44 (Cohen *d*) in accordance with calculations performed using G*power software (Version 3.1, Universität Düsseldorf). We also considered an overall dropout rate of 10% (eg, lost to follow-up). Therefore, we aimed to recruit 84 participants (28 in each study arm).

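### As written, the planning effect size of 0.44 is a baseline difference between two treated groups of a cited study, so neither 25 per arm nor the 60% power rests on a treatment effect

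*Protocol article*

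**What the plan says.** The Sample Size section gives its source as follows: "The optimal sample size was calculated on the basis of the results of a previous study [32". The only results it reports from that study are these: "The pain intensity for intervention groups was 58.2 (SD 13.93) and 64.4 (SD 13.96) at baseline, respectively [32". It continues "We estimated a sample size of 25 in each study arm", "which would yield 60% power (α=.1" in its wording, with "an effect size of 0.44" expressed as Cohen d and credited to G*Power. Ten per cent dropout brings this to 28 per arm and 84 in total.

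The Introduction sets the aim that this sample should serve: "this study first aims to investigate whether using lumbar support reduces pain in women with pregnancy-related PPGP versus controls". The Data Analysis section sets significance at P<.05 and plans Bonferroni post hoc pairwise comparisons. The article nowhere gives an expected post-treatment difference in pain, a change from baseline, or a minimal important difference.

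**The concern.** A planning effect should be the between-group difference that treatment is expected to produce, or the smallest one worth finding. The quoted means are labelled as baseline values, so their difference existed before any support was worn. If the cited study was randomised (the article does not say), the difference reflects chance. Both means also come from treated groups, whereas the first aim has an untreated comparator that receives only a leaflet. The figure is therefore wrong in timing and in contrast.

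This matters because d alone drives the sample size once alpha and power are set. At the plan's own settings (one-sided .10, 60% power) the number per arm would be 53 for an assumed d of 0.3, 20 for 0.5 and 8 for 0.8. If d is not a treatment effect, the stated power does not describe the trial's chance of answering its question, and a null result on pain cannot be read against a meaningful target.

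**Working it through.** **Inputs.** Sample Size section: means 58.2 and 64.4, SDs 13.93 and 13.96, d = 0.44, alpha .1, power 60%, 25 per arm, 10% dropout. Data Analysis section: P<.05 and Bonferroni pairwise tests. Assumed here: two-sided testing, 80% power, three pairwise comparisons, a 0-100 scale (the paragraph gives no unit) and the SD at follow-up.

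**1. Origin of 0.44.** Pooled SD = sqrt((13.93² + 13.96²)/2) = 13.945. Difference = 64.4 − 58.2 = 6.2. d = 6.2/13.945 = 0.4446. Using either SD alone gives 0.4441 to 0.4451. All lie close to the printed 0.44.

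**2. From 0.44 to 25 per arm.** n = 2(z₁₋α + z₁₋β)²/d² = 2(1.2816 + 0.2533)²/0.44² = 24.3, so 25. The noncentral t calculation also gives 25, with power 60.3%. This works only for a one-sided test: two-sided alpha .10 would need 38 per arm, and 25 would give about 46% power. Three-group ANOVA with 75 participants at alpha .10 gives 96% power for f = 0.44 and 50% for f = 0.22, so neither is the calculation used.

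**3. From 25 to 84.** 25/0.9 = 27.8, so 28 per arm; 3 × 28 = 84.

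The whole chain to 84 thus reproduces from the difference between the two baseline means, and the article offers no other source for d.

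**4. What 25 evaluable per arm can detect at the analysis level.** Detectable difference = d (noncentral t, n = 25 per arm, 80% power) × SD:

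| Two-sided level | Detectable d | SD 13.945 | SD 20 |
|---|---|---|---|
| .05 | 0.809 | 11.3 | 16.2 |
| .05/3 (Bonferroni, three pairs) | 0.944 | 13.2 | 18.9 |

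Values are points on 0-100; divide by 10 for the 0 to 10 scale in the Pain section. The range of SD is needed because 13.945 is a baseline value and no follow-up SD is given. This trial's entry threshold of 40 out of 100 restricts the spread at baseline but not at follow-up, so the follow-up SD may be larger.

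**The case against.** The cited study is not available here, and the word baseline may be a slip for a post-treatment value. That possibility stands, so it is not established that the sponsor in fact used a pre-treatment imbalance. What is established is that the paragraph, as written, derives d from values labelled as baseline. A slip would cure the timing but not the contrast, which would still be between two intervention groups.

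Baseline data are a legitimate source for an SD. Agreed: the fault lies in using the difference between the means as the effect. Even the SD has to be labelled as an assumption once it is applied at follow-up.

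Power is always conditional on an assumed effect, and the arithmetic for d = 0.44 is correct at one-sided .10. That also stands. Nothing here shows that 0.44 is optimistic; the true effect could be smaller or larger.

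A reader might set 11.3 points beside the planned 6.2 and infer that the faulty effect size understates what the trial can detect by a factor of about 1.8. The documents do not support that. At the plan's own one-sided .10 and 60% power, 25 per arm detects 0.438 × 13.945 = 6.1 points, so the ratio comes wholly from moving to two-sided .05 and 80% power. A genuine post-treatment d of 0.44 would give the same ratio. Nor can smaller detectable differences from a baseline-adjusted analysis be brought in, since the article describes no such adjustment.

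Finally, an article condenses a full protocol. But this point concerns a figure that is stated and that sets the sample size, not one that has been left out.

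**Conclusion.** The paragraph is wrong as written. The planning d of 0.44 equals the standardised baseline difference between two intervention groups of the cited study. It has no standing as the expected effect of lumbar support versus control, and the 60% power tied to it is not power for a treatment effect. This conclusion needs only the figures in the Sample Size section and the aim in the Introduction.

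No single corrected sample size can be computed, because the documents give no expected or worthwhile difference. What can be stated is the detectable difference with 25 evaluable per arm: about 11.3 points at two-sided .05 and about 13.2 with Bonferroni over three pairs, at an assumed SD of 13.9; about 16 at two-sided .05 if the SD is 20. These rest on 80% power as an assumed convention. They describe what the trial can find and are not themselves evidence of the defect. A reader might also infer that the trial is too small; without an independently sourced target difference, the documents do not settle that.

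**What to change.** 1. Check the cited study and correct the label if the quoted means are not baseline values.
2. Remove the baseline-derived d as the planning effect, together with the 60% power claim that depends on it.
3. Keep 28 per arm. Restate the paragraph as the difference in pain, lumbar support versus control at a named follow-up time, that 25 evaluable per arm can detect at the significance level of the Data Analysis section. State the power, the sidedness and whether Bonferroni is applied. Give the SD as an assumption with a range, as in the table above.
4. Beside it, give an expected or clinically worthwhile difference taken from an independent source. If the trial cannot detect that difference, say so. The detectable difference should not be declared worthwhile after the fact because 25 per arm happens to reach it.

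The cost is a source check and one rewritten paragraph; restating at fixed n adds no participants. The downside is that the stated target becomes larger and the power statement less favourable. If the independent difference turns out smaller than the detectable one, the sponsor must either accept that limit openly or reconsider the sample size.

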### Data Analysis

All data will be saved with identification codes to maintain confidentiality. Every effort will be made to follow up on all subjects by the examiner. All enrolled participants, including those who do not complete treatment, will be included in the analysis on the basis of the intention-to-treat principle. Missing data will be replaced by the mean imputation technique, in which the mean of the observed values will be calculated and reported. Descriptive statistics will present demographic characteristics and outcome measures for each intervention group. Multivariate ANOVA will be used to test between- and within-group differences. Data will be controlled for outliers and checked for the normality and homogeneity assumptions. Post hoc (Bonferroni) tests will be conducted to report pair-wise comparisons. SPSS (version 17.0; SPSS, Inc) will be used for statistical analysis, and statistical significance will be set at a *P* value of <.05.

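### The stated 60% power is calculated at α=.1, but the analysis tests at P<.05 with Bonferroni pairwise comparisons, so the figure does not describe the planned decision rule

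*Protocol article*

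**What the plan says.** The Sample Size section takes two group values from an earlier study: "The pain intensity for intervention groups was 58.2 (SD 13.93) and 64.4 (SD 13.96) at baseline, respectively". From these it obtains Cohen d = 0.44. It then says: "We estimated a sample size of 25 in each study arm, which would yield 60% power (α=.1) and an effect size of 0.44". Allowing for 10% dropout, 25 becomes 28 per arm, or 84 in total. The section names G*Power, but neither the test selected in it nor the sidedness.

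The Data Analysis section fixes a different rule. A multivariate ANOVA tests differences between and within groups, "Post hoc (Bonferroni) tests will be conducted to report pair-wise comparisons", and "statistical significance will be set at a *P* value of <.05". The randomisation section allocates 1:1:1 to pelvic support, lumbar support and control, so there are three pairs of arms.

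**The concern.** Both significance levels are printed in the same article, and they disagree. The sizing α of .1 is twice the analysis α of .05. It is six times the per-pair level if Bonferroni divides by three (.05/3 = .0167). The sizing makes no allowance for the three pairwise comparisons, yet both aims in the Introduction are pairwise contrasts: lumbar support against control on pain, and lumbar against pelvic support on disability and sensorimotor outcomes.

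A reader who takes 60% at face value will overestimate what a non-significant contrast shows. The Discussion expects the results to inform clinical decisions between the supports, so a null result could be read as no benefit when the trial had little chance of detecting an effect of the size used for planning.

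**Working it through.** **Inputs.** From Sample Size: n = 25 evaluable per arm (28 recruited), α = .1, power 60%, means 58.2 and 64.4, SDs 13.93 and 13.96. From Data Analysis: α = .05 with Bonferroni pairwise tests. From the randomisation section: three arms, hence three pairs. Assumption: the Bonferroni divisor is 3, which the article implies but does not state.

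**Effect size.** The pooled SD is √[(13.93² + 13.96²)/2] = 13.945, and (64.4 − 58.2)/13.945 = 0.445, stated as 0.44. This reproduces.

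**Dropout.** 25/0.9 = 27.8, rounded up to 28; 3 × 28 = 84. This reproduces.

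**The stated 60%.** For a two-sample t test, the noncentrality is d√(n/2) = 0.44 × √12.5 = 1.556 with 2n − 2 = 48 df. Power is the probability that a noncentral t exceeds the critical value (plus the negligible opposite tail if two-sided). At one-sided .1 the critical value is 1.299 and power is 60.3%. The smallest n per arm that reaches 60% is exactly 25.

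**The same d under other rules.** With n = 28 the noncentrality is 0.44 × √14 = 1.646 with 54 df.

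| Rule (single pairwise contrast, one time point, no covariate) | Power, 25 per arm | Power, 28 per arm | n per arm for 60% |
|---|---|---|---|
| One-sided .10 | 60% | 64% | 25 |
| Two-sided .10 | 46% | 49% | 38 |
| Two-sided .05 | 33% | 37% | 52 |
| Two-sided .05/3 | 19% | 21% | 74 |
| One-sided .05 | 46% | 49% | 38 |
| One-sided .05/3 | 27% | 30% | 60 |

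Using the pooled three-arm error (72 df) changes little at n = 25: 34% at two-sided .05 and 19% at .05/3.

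**Omnibus test.** A one-way F test at .05 with N = 75 has 26% power if the third mean lies midway (f = 0.44/√6 = 0.18), 33% if two arms coincide (f = 0.44√2/3 = 0.207), and 37% at f = 0.22. It does not restore 60% either.

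**Detectable difference.** With 25 per arm, the d giving 80% power is 0.81 at two-sided .05 and 0.94 at two-sided .05/3.

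**Sensitivity to correlation (assumed values; the article gives none).** Adjusting for baseline with correlation r changes d to d/√(1 − r²). At r = .5 this is 0.44/0.866 = 0.508, and power with 25 per arm is 42% at two-sided .05 and 26% at .05/3. At r = .3 the figures are 36% and 21%; at r = .7 they are 57% and 39%. If the effect is also constant over T2 to T4, those three values are averaged and all correlations are .5, the residual variance is (1 + 2 × .5)/3 − .5² = 0.417. Then d becomes 0.44/√0.417 = 0.682, and power is 66% and 48%.

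**The case against.** Three points on the other side have force.

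First, a reader might infer that 60% can arise only from a one-sided t test. The article does not support that, because it does not name the test. A repeated-measures ANOVA for the between-groups effect, with f = 0.22, three groups, N = 75, two measurements, an assumed correlation of .5 and α = .1, has λ = 75 × 0.22² × 2/1.5 = 4.84 and also gives 60.3% power. The t test remains the likelier source, since the section quotes Cohen d and 25 is exactly the n it requires. But it is an inference.

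Second, a reader might infer that the trial's real power is 19% to 33%. That is also too strong. Those figures are for an unadjusted contrast at one time point, and the plan is a multivariate ANOVA on data from up to four time points. The sensitivity figures show that power could be materially higher, and in the averaged case above 60% before Bonferroni. The 33% also leaves out the Bonferroni step that the plan includes; the figure with that step is 19%. Against this, the sizing claims no gain from repeated measures and gives no correlation to support one.

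Third, d = 0.44 comes from baseline means in another study and is not shown to be an expected treatment effect. The power figures here are conditional on it, as the stated 60% is.

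It is also fair that 60% power and α=.1 are openly declared, and that the step from 25 to 28 to 84 is correct. The fault is a mismatch between two sections, not an arithmetic slip. None of these points removes the mismatch.

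**Conclusion.** The point holds as an inconsistency that makes the power statement wrong as written. The 60% is attached to α=.1 without multiplicity correction, and the trial will decide at P<.05 with Bonferroni pairwise tests.

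For d = 0.44 and 25 per arm, the like-for-like figures are 33% at two-sided .05 before Bonferroni and 19% at .05/3. They rest on four assumptions: P<.05 is two-sided, Bonferroni divides by three, the contrast is at a single time point, and there is no covariate. Reading P<.05 as one-sided gives 46% and 27%, still short of 60%. Gains from baseline adjustment or repeated measures are possible, but the article gives no basis for their size.

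**What to change.** Keep 28 per arm and rewrite the power sentence in Sample Size so that its test, sidedness, α and Bonferroni divisor are those of Data Analysis. For example: with 25 evaluable per arm and d = 0.44, a two-sided two-sample t test has about 33% power at .05 and 19% at .05/3 (Bonferroni over three pairs); the difference detectable with 80% power is about 0.81 SD and 0.94 SD respectively. A higher power may be stated if it comes from a named repeated-measures or baseline-adjusted analysis with a justified correlation. Give the detectable difference in SD units, because the article scores pain on 100 mm for eligibility and on 0 to 10 for the outcome.

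Add that a non-significant contrast will be reported with its confidence interval as inconclusive, not as evidence of no benefit.

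The cost is one reworded paragraph and a less favourable stated power. No further participants are needed.
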